### **5. Recruitment Strategy**

Apparently healthy women of child-bearing age (18-45y) or male (blood donors only) volunteers (age 18-65y) with low iron stores (serum ferritin  $\geq 15 \leq 60 \mu\text{g/L}$ ) will be screened until 16 participants have been recruited. Based on previous experience with similar studies, dropouts and unsuccessful blood collection will mean that only 13 complete sets of data will be obtained for analysis. This is, however, sufficient for this study (see power calculation, section 14.1).

Participants will be recruited from the Norwich Research Park (NRP) and the surrounding Norwich area. Advertisements will be placed on the University of East Anglia (UEA) website, NRP newsletters, distributed via email to UEA staff and students (Annex 2), and placed on notice boards at IFR, the John Innes Centre (JIC), TGAC, UEA schools, local supermarkets, and other suitable locations (e.g. gyms) inviting anyone interested in receiving information about the study to contact named researchers by telephone or e-mail.

Volunteers who meet the basic inclusion criteria (section 7), will be sent a participant information sheet (PIS) (Annex 3) which will include a response form and a freepost envelope with which to reply if they are interested in participating in the study.

There are no arrangements for participants who might not understand verbal or written information given in English as the cost of translating study information would be prohibitive.

This is a small study and it is expected that sufficient volunteers fluent in English will be recruited from across the Norwich Research Park. However, should there be any doubt regarding a volunteer's understanding of what the study involves then they will not be recruited. This assessment will be made by the study scientist at the stage of discussion about the study.

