#### **1.2.1. Study design**

The study design and outline are presented in Figures 1 and 2. This study is designed as a randomised, single blinded, cross-over trial with participants randomly allocated into two groups: A (n= 8 volunteers) and B (n=8 volunteers). For statistical power of this study please refer to section 14.1. By administration of test meals 1 and 4 scientist will investigate the possible protective effect of alginate on iron absorption (primary outcome). By administration of test meal 2 and 3 the research team will investigate whether alginates can bind calcium (a well-known iron inhibitor) *in vivo*, thus diminish the potential negative effect of calcium on iron absorption (secondary aim).

Only half (8) of the volunteers will undergo treatments including calcium. Therefore group A will undergo all 4 tests, whereas group B will undergo 2 out of 4 tests.

This study will be undertaken to compare the absorption of iron (approximately 20mg) added to cola jelly (200ml) as ferrous gluconate incorporated into alginate beads (approx. 22.2g) (test meal 1), with iron at the same dose given as ferrous gluconate in a commercially available capsule along with a diet cola drink (200ml), (test meal 4). The third test for group A only (test meal 3) will involve consuming iron incorporated into the alginate beads (approx 22.2g) added to cola jelly (200ml), followed by 2 capsules, each filled with 300mg commercially available calcium phosphate powder (Freedav  
vitamins, USA,

<http://www.freedavitamins.com/index.php?p=product&id=120&parent=10> )

(600mg in total) in the form of calcium phosphate. Cook *et al* has shown that this dose and form of calcium was the most effective in iron inhibition. The addition of calcium will determine whether the alginate barrier can reduce or prevent the inhibitory effect of calcium on iron absorption. The fourth test (test meal 3) will involve consuming cola jelly (200ml), a ferrous gluconate capsule (approx. 20mg) and two calcium phosphate capsules (300mg of calcium in each capsule) followed by a diet cola drink (200ml).

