### **12.1. Storage of the data**

Electronic data stored within the UEA will be account password protected. Electronic data transferred via email is encrypted by the UEA web server. Only study scientists and appointed nurses will have access to the coded

information. It is expected that up to 50 potential volunteers will be screened in order to recruit a total of 16 volunteers successfully completing the study.

[name], academic supervisor will act as custodian of the data generated in this study.

A hard copy of the datasheet linking names and addresses with code numbers will be kept in a locked filing cabinet at UEA MED with access restricted to the academic supervisor [name] and chief investigator [name]. Anonymised participant data will be stored on the secure network at UEA and CRTU and will not be stored on any external drives (including desk top C drives, laptops or external storage devices). Access to the files will only be accessible to the staff associated with this project. Manual files containing the source data will be kept within the CRTU in locked storage cabinets during the intervention and once the intervention will be completed, the data will be stored in locked archive storage, located at the MED building at UEA for 5 years after the completion of the study. In addition, coded 'non-identifiable' patient data will be kept in secure storage, with access limited to study staff, and the information will be archived in locked file cabinets for 5 years and then destroyed appropriately. Biological samples will be stored as cell-free extracts for analysis and retained at the study sites to be accessed by study staff for 5 years from collection and then destroyed using standard biohazard procedures in place at the Biomedical Research Centre at the UEA.

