### **14.1. Statistical power**

Each volunteer will act as his/her own control, which will minimise the number of subjects required. The assumptions made for the power calculation to estimate the number of volunteers are that a difference of 2.5% in iron absorption between the 2 tests (primary outcome, test meal 1 and test meal 4) will be nutritionally significant. A minimum of 12 volunteers would be required to complete the study to detect a difference of 2.5% at a significance level of 0.05 for 80% power.

For the secondary aim, a minimum of 8 volunteers would be required to detect a significant difference in iron absorption of 3.3% between a test meal containing 20mg of iron as iron gluconate with calcium and a test meal containing 20mg of iron as iron gluconate with calcium and alginate beads (test meals 2 and 3). This assumes a power of 80%, a level of significance of 0.05 and standard deviation of differences (within pairs) of 2.8%

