### **14.2. Statistical method**

The primary outcome measure is the difference in iron (ferrous gluconate) absorption when consumed in a form of iron incorporated into alginate beads compared with the same amount of iron in an unprotected form i.e. not in alginate beads. The secondary outcome measure is the difference in iron

(ferrous gluconate) absorption when consumed in presence of calcium in a form of iron incorporated into alginate beads compared with the same amount of iron not in alginate beads in presence of calcium.

Paired, two-tailed Student's t test will be used to assess any significant differences in absorption (for the primary and secondary outcome measure). This method was found to be appropriate when assessing iron absorption in previous studies conducted at the Institute of Food Research.

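### The secondary (calcium) comparison needs all 8 group A volunteers to give a usable pair, so the 13 complete datasets called sufficient in section 5 support the primary aim only

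*Protocol*

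**What the plan says.** The power statement for the secondary comparison is in section 14.1: "For the secondary aim, a minimum of 8 volunteers would be required to detect a significant difference in iron absorption of 3.3" percentage points between the two calcium meals. Its inputs follow: "This assumes a power of 80%, a level of significance of 0.05 and standard deviation of differences (within pairs) of 2.8" per cent. Section 14.2 names the test: "Paired, two-tailed Student's t test will be used to assess any significant differences in absorption".

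Section 1.2.1 fixes who supplies these data. Volunteers are "randomly allocated into two groups: A (n= 8 volunteers) and B (n=8 volunteers"), and "Only half (8) of the volunteers will undergo treatments including calcium". Sections 8.2 and 8.3 place the two calcium meals at visits 4 and 5, with visit 5 for group A only. Section 8 provides 16 numbered envelopes.

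Section 5 stops recruitment at 16, anticipates dropouts and failed blood collection, and concludes that "only 13 complete sets of data will be obtained for analysis. This is, however, sufficient for this study", citing section 14.1 without saying which of the two aims is meant. Section 12.1, on data storage, gives a different count: up to 50 people screened to obtain "a total of 16 volunteers successfully completing the study".

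**The concern.** The number required for the secondary aim equals the number allocated to it. Section 5 plans for the loss of 3 datasets in 16 and treats the remainder as enough, but it sets one total of 13 against a section with two separate requirements. The primary comparison draws on both groups; the secondary draws on group A alone. A total of 13 does not show how many meal 2/3 pairs survive.

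At stake is how a non-significant calcium result will be read. The secondary aim has its own hypothesis in section 4 and its own power calculation. A reader would judge a null result against 80% power at 3.3 points, when at the protocol's own loss rate the comparison probably has less. The primary analysis, the type I error and the validity of the estimate are not affected.

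**Working it through.** **Inputs.** Difference 3.3 points, SD of paired differences 2.8, two-sided alpha 0.05, power 80%, minimum 8 (section 14.1). Two-tailed paired t test (section 14.2). Group A = 8, group B = 8 (section 1.2.1). Complete sets expected: 13 of 16, so 3 lost and a loss rate of 3/16 = 18.75% (section 5).

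**Formula.** For n pairs, the test statistic follows a noncentral t distribution with n − 1 degrees of freedom and noncentrality (3.3/2.8) × √n. Power is the probability that it falls outside the two-sided 5% critical values.

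**Reproducing the plan's figure, and power after losses.** The detectable difference is the one that gives 80% power with SD 2.8.

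| Pairs | Noncentrality | Power at 3.3 points | Detectable difference |
|---|---|---|---|
| 8 | 1.179 × √8 = 3.33 | 81.5% | 3.24 |
| 7 | 1.179 × √7 = 3.12 | 73.9% | 3.56 |
| 6 | 1.179 × √6 = 2.89 | 64.0% | 4.02 |
| 5 | 1.179 × √5 = 2.64 | 51.6% | 4.71 |

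The stated minimum of 8 is right: it is the smallest n that reaches 80% with the named test. It also contains no spare pair.

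**Loss assumption.** The protocol does not split the 3 losses by group or visit. I assume that they fall at random over the 16 volunteers and that each loss in group A costs a meal 2/3 pair.

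- Expected pairs: 8 × 13/16 = 6.5.
- Chance of k losses in group A: C(8,k) × C(8,3−k) / C(16,3), with C(16,3) = 560.
  - k = 0: 56/560 = 10%
  - k = 1: 224/560 = 40%
  - k = 2: 224/560 = 40%
  - k = 3: 56/560 = 10%
- Average power: 0.10 × 81.5 + 0.40 × 73.9 + 0.40 × 64.0 + 0.10 × 51.6 = 68.5%.

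**Alternative assumption.** If each volunteer is lost independently with probability 3/16, the chance that all 8 remain is (13/16)^8 = 19%, and average power is 67.8%. The chance of keeping all 8 depends on the loss model; the average power of about 68% hardly does.

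**Primary aim.** 13 exceeds the minimum of 12 stated in section 14.1, so the sentence in section 5 is consistent with that figure.

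**The case against.** A reader might infer that the 80% power is certainly not delivered, that section 14.1 is miscalculated, or that the protocol rules out replacement. The documents support none of these.

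- Section 14.1 is conditional. It says how many volunteers would be needed, and its arithmetic is correct. It does not promise that 8 will complete.
- Section 5 does not say where the losses fall. If all 3 fall in group B, the secondary comparison keeps its 8 pairs. Random loss is my assumption.
- A complete set is not the same as a usable secondary pair. In group A, failed sampling confined to visit 3, or a loss only at visit 6, leaves an incomplete set but an intact meal 2/3 pair. On this ground 6.5 pairs could be too low. In the other direction, group A has four cannulation days against two in group B, so it has more opportunity for loss.
- The protocol is silent on replacement. Sixteen envelopes and a target of 16 recruits suggest none is planned, but nothing forbids it. Section 12.1 can be read as aiming for 16 completers, which would remove the shortfall. That remark is incidental, has no procedure behind it and conflicts with the more explicit account in section 5. The documents do not settle which is intended.

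These points limit the claim to an expected shortfall under stated assumptions. They do not restore the sufficiency statement for the secondary aim: it would hold only if the losses happened to spare every group A pair, and the protocol gives no reason to expect that.

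**Conclusion.** The point stands as an internal inconsistency in the stated power and should be fixed. The secondary comparison has no margin for loss, and the statement that 13 complete sets suffice holds against the primary aim's stated minimum but not, in general, for the secondary aim. If the 3 losses are spread at random and each one in group A costs a pair, the likely outcome is 6 or 7 pairs, power between 64% and 74% at 3.3 points, and 80% power only for about 3.6 to 4.0 points. All 8 pairs survive with probability about 10%, or 19% under independent losses. These figures take the protocol's SD of 2.8 as given and would shift if losses concentrate in one group or at visits outside the meal 2/3 pair.

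**What to change.** 1. In section 5, limit the sufficiency statement to the primary outcome.
2. In section 14.1, keep the calculation for 8 pairs and add the power or detectable difference at 6 to 7 pairs (74% with 7 and 64% with 6 at 3.3 points; about 3.6 to 4.0 points for 80%), with the loss assumption written beside it.
3. Reconcile the 13 complete sets in section 5 with the 16 completers in section 12.1, and say whether lost group A volunteers are replaced.

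Items 1 and 2 cost only wording. Item 3 is also wording unless replacement is chosen, which would need further allocations beyond the 16 envelopes and further study days.

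An optional design change is to allocate 10 to group A and 6 to group B. Expected pairs become 10 × 13/16 = 8.1, and study days rise from 8 × 4 + 8 × 2 = 48 to 10 × 4 + 6 × 2 = 52. This is a trade-off and not a guarantee. Fewer than 8 pairs would still occur with probability C(10,3)/C(16,3) = 120/560 = 21% under three random losses, or about 28% under independent losses.

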## **6. Volunteer Screening**

### **6.1. Visit 1. Initial Interview**

Apparently healthy women or men (blood donors only) potential volunteers who respond positively to the advertisements and the PIS (via email, telephone or post) will be asked to visit the CRTU for an informal meeting to receive further information about the study. Responders will be invited to the meeting on an individual basis to ensure privacy and a study scientist will explain the details of study participation. During the meeting the study scientist will follow the interview script (annex 4), which will act as a prompt to

the scientist to ensure that the volunteer understands his/her role in taking part in this study. The script will not be followed word-for-word but will simply act as a reminder to the study scientist to make sure all aspects of the study have been fully explained to the potential participant. Volunteers who meet the basic inclusion and exclusion criteria (section 7) will be encouraged to ask any questions they may have about the study prior to making any commitment and will be given a minimum of 72 hours (3 days) to consider whether they wish to participate in the study. In addition they will be asked to select a meal (from the Catering Direct packed lunch menu) which they would like to consume after the screening visit. During the consideration period the volunteers will not be contacted by any member of the research team. If, following the period of consideration, the volunteer wishes to participate in this study they will be advised to contact the named researchers to arrange for a clinical screening visit at the CRTU. If the volunteers are very keen to participate in the study and ask to book a screening date at the meeting, this can be arranged with the appointment booked for after the minimum of 72 hours consideration period.

## **6.2. Visit 2. Consent and screening**

Prior to being accepted onto the study, all volunteers who are willing to participate following the initial informal meeting will be clinically screened to ensure that biochemical indices fall within the standard reference ranges for age and sex. Volunteers will be invited to attend a clinical screening visit at the CRTU after an overnight fast of at least 8 hours. They will be advised to drink water during the fasting period. Potential participants will also be reminded to bring details of any regular medication or dietary supplements they take (i.e. dose taken, name of medication).

On arrival, the study scientist will go through the consent form with the volunteer and encourage any questions they may have at this stage. Volunteers will then be asked to sign a consent form agreeing to participate in the study (Annex 5). A copy of this form will be given to the volunteer to keep. Subsequently, a researcher along with an experienced CRTU nurse will

complete a basic health questionnaire (Annex 6) and collect information about weight and height. The CRTU nurse will obtain and record blood pressure measurements, pulse and BMI. A single venous blood sample (10ml) will also be taken by a CRTU nurse for assessment of iron status and to confirm lack of chronic inflammation/infection (full blood count: Wbc, Rbc, Hb, Hct, MCV, MCH, platelets, Neutrophils, Lymphocytes, Monocytes, Eosinophils, Basophils, fasting glucose and ferritin). In addition C reactive protein (CRP) assessment from baseline blood samples will be performed on each experimental day to establish if serum iron appearance could be affected by inflammation. The blood will be analysed at an accredited pathology laboratory at the NNUH, Norwich. Once all clinical procedures are completed, the volunteers will be offered and encouraged to have a meal which they selected during the screening visit.

During that meeting volunteers will also be asked to select a meal from the Catering Direct (UEA) 'Scholars packed lunch' list which they would like receive at the completion of experimental days. This information will be recorded by the study scientist.

Volunteers will be excluded if their BMI is <18.5 and >30 or their blood pressure measurements are >160/100. Volunteers will also be excluded from further participation if the serum ferritin is less than 15ug/L (indicates iron deficiency) or greater than 60µg/L (The full list of inclusion / exclusion criteria are given in section 7)

Blood screening results will be examined by an experienced CRTU nurse who will advise the study scientist if all screening parameters are within the normal range for sex and age, and therefore whether the participant can take part in the study. In addition, screening results will be forwarded to the volunteers G.P. If any of the parameters (apart from ferritin values of  $\geq 15 \leq 60 \mu\text{g/L}$ , study specific requirement) fall outside the normal range the results will be forwarded to the study medical advisor [name], UEA. [name] will then be contacted by a study scientist and asked whether the results could affect the study data or have implications for the health of the volunteer, and therefore whether inclusion, exclusion or re-screen is appropriate.

The GPs of those successfully recruited onto the study will be informed of their patient's participation in the study by letter (Annex 7) and will be sent copies of all clinical screening results (Annex 8, Annex 9). If the CRTU nurse advises the study scientist that blood screening results are abnormal, the volunteer will be asked to contact their G.P. Volunteers will be informed of flagged blood results by a telephone call and letter (Annex 11) advising them to speak to their GP to discuss the results. Non-clinical study scientists will not discuss clinical results with individual volunteers. All abnormal clinical results obtained during the study from fresh samples (not stored), that have been analysed at an accredited laboratory and which fall outside the standard reference ranges, will also be sent to the GP (Annex 10).

The volunteer will agree to this information being sent to the GP by signing the consent form.

During the screening interview the study scientist will also provide instructions on keeping a 1-day food diary to record the "pre-test diet" in preparation for the first experimental day (VISIT 3). Volunteers will be asked to repeat the same pre-test diet prior to each experimental day. In cases where any food or drink was consumed in addition to the pre-test diet or was forgotten to be eaten, volunteers will be asked to note it down in the Record of Differences Diary at the end of the food intake diary (Annex 12). During that meeting participants will also receive instructions with regard to undertaking 10 hour overnight fast. They will be encouraged to have a meal no later than 9pm on the night prior to each experimental day and aim to arrive at the CRTU at around 8:00 am the next morning.

## **7. Inclusion / Exclusion Criteria**

The Inclusion Criteria for this study are:

- Apparently healthy women (aged 18-45) or male blood donors (aged 18-65)
- Serum ferritin value of  $\geq 15 \leq 60 \mu\text{g/L}$

- BMI >18.5 or < 30
- Willingness to consume jelly prepared with the use of gelatine from an animal source

The exclusion criteria for this study are:

- Diagnosed with a long-term illness requiring active treatment, e.g. diabetes, cancer, cardiovascular disease
- Currently smoking or stopped smoking in the last 12 months
- Previous or current GI disease
- Any significant co-morbidity
- Previous GI surgery
- Blood donation within the previous 3 months assuming that volume taken is above 500ml in a 4-month period
- Blood transfusion within the last 3 months
- The results of the screening tests indicate unsuitability to take part in the study
- Related to someone in the study team i.e. spouse, partner or immediate family member
- Regular prescribed medication that may interfere with iron metabolism
- Regular use of antacids and laxatives (at least once a week)
- Women who are pregnant or less than 12 months since giving birth
- Women who are breast feeding
- Vitamin supplements with or without minerals if taken more than once a week, and unwillingness to discontinue occasional use for the duration of study
- Unwillingness to discontinue use of herbal supplements for the duration of study
- Unwillingness to consume jelly prepared with animal source gelatine
- Use of antibiotics within four weeks prior to study start

- Parallel participation in another study which involves dietary interventions or sampling of blood that may increase the volume taken above 500ml in a 4-month period
- Asthma requiring treatment within the last two years
- Results of clinical screening which indicate a health problem which could compromise the well-being of the volunteer if they participated or which would affect the study data.

